### Objectives

The primary objective of this study is to compare EUS-FNA versus EUS-FNB for the diagnostic yield (%) of malignancy [13]. The secondary objectives are to compare EUS-FNA versus EUS-FNB for 1) the overall diagnostic yield (%) from solid lesions; 2) the diagnostic yield (%) from pancreatic and nonpancreatic solid lesions, 3) the crossover diagnostic yield (%), and 4) the sample quality obtained by either the slow-pull or suction approaches, respectively.

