### Interventions

Patients will be allocated randomly into group A (EUS-FNA, n = 204) or group B (EUS-FNB, n = 204). Group A patients will be examined with the 22G EchoTip Ultra needle, and group B will be examined with the 22G EchoTip ProCore needle.

The procedure will be performed under deep sedation according to the principles of “monitored anesthesia care.” The patients will be anesthetized with intravenous administration of propofol by trained anesthetists. All patients will receive oxygen during the procedures; blood pressure and heart rate will be monitored. Once the lesion is evaluated by EUS, the echoendoscopist will select the shortest pathway, while avoiding blood vessels, to reach the lesion. Under real-time visualization, each lesion will be punctured with four needle passes. To eliminate technical biases, the same procedure for obtaining samples will be applied to each patient undergoing EUS-FNA or EUS-FNB.

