### Statistical analysis

#### Sample size

We assumed that the diagnostic yield of malignancy for EUS-FNA was 80 % [23] versus 93 % for EUS-FNB [11, 13]. Because approximately 70 % of patients are expected to be diagnosed with malignancy [9], the sample size should be 342, with a power of 85 % and a two-sided significance level of 5 %. Considering 20 % of patients will be lost to follow-up, the estimated patient number in this trial should be 408.

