#### Data analysis

A two-tailed distribution will be used and a *P*-value < 0.05 is considered statistically significant. Continuous variables will be measured as mean (range) and standard deviation using *t* tests or Wilcoxon rank-sum tests. Categorical variables will be measured as the count and percentage using the χ2 test. The diagnostic yield will be described as a proportion using the χ2 test; the blood contamination and cellularity in specimens with slow-pull and suction will be divided into three levels (Grade A, Grade B, and Grade C), and McNemar’s test for correlated proportions will be used. All analyses will be performed with SAS version 9.2.

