The success of EUS-FNA is associated with several factors, including appropriate methods of biopsy, sample preparation, and onsite cytopathological interpretation [31]. The onsite cytopathological interpretation may not always be available during EUS**-**FNA procedures; therefore, appropriate methods of biopsy and sample preparation are very important. Some echoendoscopists use slow-pull, and others use constant suction. Suction with a self-retracting syringe will likely bring more cellularity but also more blood. In this trial, the echoendoscopist will use both methods (slow-pull and constant suction) on each lesion and, hopefully, will be able to draw a clear conclusion on selecting which biopsy method should be used for which procedure. Furthermore, standard procedures and sample preparation methods will be used to process all types of biopsy samples. For example, after the needle has been inserted into the mass, for both FNA and FNB, the needle will be moved back and forth 20 times within the lesion to collect specimens. The specimens will be expelled from a needle in three steps: step 1, which involves pushing the stylet into the needle; step 2, which involves flushing the needle with 0.1 ml saline; and step 3, which involves filling the needle with 2 ml of air.

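### McNemar's test, a paired two-category test, is assigned to three ordered grades with no cut-point or extension named, so the within-lesion slow-pull versus suction analysis is not fixed.

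*Protocol article*

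**What the plan says.** The Data analysis section covers two graded outcomes of the within-lesion comparison, blood contamination and cellularity. For these the plan reads: "divided into three levels (Grade A, Grade B, and Grade C), and McNemar’s test for correlated proportions will be used". The level is set in the same section: "A two-tailed distribution will be used and a *P*-value < 0.05 is considered statistically significant".

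The Histology and Cytology assessment criteria define the grades as ordered. Blood contamination is A below 25 %, B 25-50 % and C above 50 % of the slide. Cellularity runs from satisfactory (A) through adequate (B) to unsatisfactory (C). The document nowhere collapses the grades to two categories, gives a cut-point or names an extension of McNemar's test.

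The pairing comes from the design, as the Discussion describes it: "the echoendoscopist will use both methods (slow-pull and constant suction) on each lesion". The same paragraph expects a direction: "Suction with a self-retracting syringe will likely bring more cellularity but also more blood". The Technique section gives two passes per method in each lesion (first and second slow-pull, third and fourth suction), labelled by pass.

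**The concern.** The sentence fixes both the scale and the test, and the two do not match. An analyst has to choose between A against B+C, A+B against C, and a 3x3 test. These choices can differ on whether the same data are significant. None of them uses the order of all three grades, although the expected effect is a movement up or down that order. The Discussion hopes this comparison will show which sampling method suits which procedure, so the way it is tested should be settled before the grades are seen.

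**Working it through.** **The plan's own figure.** The document gives no sample size or power for slow-pull versus suction. Its only calculation is for the primary endpoint: "We assumed that the diagnostic yield of malignancy for EUS-FNA was 80 % [23] versus 93 % for EUS-FNB". With unpooled variance, (1.960 + 1.036)² × (0.80×0.20 + 0.93×0.07) / 0.13² = 8.978 × 0.2251 / 0.0169 = 119.6 malignant patients per arm. Then 2 × 119.6 / 0.70 = 341.7, which gives the stated 342. That figure reproduces and has no bearing on the paired comparison.

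**The candidate tests.** Let n_ij be the number of lesions with slow-pull grade i and suction grade j.
- McNemar at one cut: (b − c)² / (b + c), 1 df, where b and c are the two discordant counts after collapsing.
- Bowker: sum over i<j of (n_ij − n_ji)² / (n_ij + n_ji), 3 df. It tests symmetry and ignores order.
- Stuart-Maxwell: d′V⁻¹d on the differences in marginal counts, 2 df. It tests marginal homogeneity and ignores order.
- Paired ordinal score test: (Σ s)² / Σ s², 1 df, where s is the within-lesion difference of grades scored 0, 1, 2.

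**Inputs.** From the document: 204 patients per arm (Interventions) and two-sided 5 %. Assumed, because the document gives none: the grade distributions, one grade per technique per lesion, and a latent bivariate normal model with correlation 0.3. There were 20,000 replicates per scenario.

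**What each cut sees.** The change at each cut follows from the assumed margins, and the change in mean score is the sum of the two cut changes.
1. Overall shift, 45/35/20 to 37/37/26 %: A falls 8 points, A+B falls 80 − 74 = 6; mean score rises 0.89 − 0.75 = 0.14.
2. A/B boundary only, 45/35/20 to 35/45/20: 10 and 0; mean score rises 0.10.
3. B/C boundary only, 45/35/20 to 45/27/28: 0 and 8; mean score rises 0.08.
4. Rare grade C, 60/32/8 to 51/38/11: 9 and 3; mean score rises 0.12.

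**Power at 204 pairs, and how often exactly one of the two cuts is significant:**

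| Scenario | A v B+C | A+B v C | Bowker | Stuart-Maxwell | Ordinal | Cuts differ |
|---|---|---|---|---|---|---|
| 1 | 45 % | 36 % | 38 % | 44 % | 55 % | 38 % |
| 2 | 63 % | 5 % | 49 % | 56 % | 34 % | 62 % |
| 3 | 5 % | 54 % | 45 % | 52 % | 21 % | 54 % |
| 4 | 53 % | 20 % | 38 % | 45 % | 54 % | 46 % |

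**Sensitivity.**
- Grades 45/30/25 %, correlation 0.4 and a uniform latent shift of 0.2 SD, at 204 pairs: ordinal 57-58 %, McNemar 45-46 % and 39-42 %, Bowker 39-40 %; the cuts differ in about 37 % of trials.
- Scenario 1 with correlation 0.6, at 204 pairs: McNemar 56 % and 44 %, Bowker 54 %, Stuart-Maxwell 61 %, ordinal 72 %.
- 408 pairs: ordinal against Bowker is 84 v 69 % in scenario 1, and 86 v 73 % under the 0.2 SD shift.

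**No true difference.** Each cut alone rejects in about 5 % of trials. At least one of the two rejects in 9-10 %.

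**The case against.** The strongest reply is that a condensed article may use McNemar's name as shorthand. Bowker's test is its generalisation to larger tables and is often called McNemar-Bowker. Stuart-Maxwell is another natural reading where correlated proportions have three levels. Naming the extension is a detail that articles often leave to the full protocol or SAP. This stands in part: a reader might infer that the analysis cannot be run at all, and that goes too far. But the article does not leave the matter open. It names a scale and a test that do not fit, and any SAP would have to reinterpret or depart from that sentence.

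The ordinal test is also not uniformly better. When one boundary alone moves, it falls behind Bowker (34 v 49 % and 21 v 45 %). With rare grade C, McNemar at A v B+C matches it (53 v 54 %). The Discussion supports a direction but not an equal shift at both boundaries. This stands, and it limits the power argument to an overall shift.

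Three stronger readings are not supported:
- **Contradictory findings.** A reader might infer that the two cuts could point in opposite directions. Under the uniform 0.2 SD shift, both cuts were significant in opposite directions in 0 of 10,000 simulated trials. Disagreement means significant against not significant.
- **Inflated type I error as planned.** The 9-10 % arises only if both cuts are tried and the better one kept. Nothing in the document says this will be done.
- **The whole sample-quality objective left without a valid test.** The fourth secondary objective compares the needles on "the sample quality obtained by either the slow-pull or suction approaches, respectively". As worded this is a between-needle comparison, which the χ2 test named for categorical variables can cover. McNemar serves only the within-lesion question, for blood contamination and cellularity.

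**Conclusion.** The point holds in a limited form. The stated test does not fit the stated scale, and the text does not say which workable substitute is meant. Under an assumed overall shift at 204 pairs, those substitutes give about 36-46 % power against about 55-58 % for a paired ordinal test, and the choice of cut alone changes the significance verdict in roughly 37 % or more of simulated trials. These sizes depend on assumed grade distributions and correlations, and the power ranking reverses if the effect sits at one boundary. That the analysis is unspecified depends on no assumption. The primary analysis and the between-needle comparison are unaffected, so this is a correction that should be made, not one on which the trial's main result depends.

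**What to change.** Replace McNemar's test for the A/B/C grades with one prespecified paired ordinal test that matches the direction expected in the Discussion. A Cochran-Mantel-Haenszel row-mean-score test with lesion as stratum is suitable. It can use both passes per technique; the grade scores should be stated, since equal spacing is itself a choice. If a Wilcoxon signed-rank test is preferred, first state how the two pass grades per technique are combined into one, because otherwise the within-lesion difference is undefined. Keep McNemar's test for binary paired outcomes only.

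The downside is lower power if the effect is confined to one grade boundary, so also report the full 3x3 table of slow-pull by suction grades. If the sponsor prefers a general alternative, name Bowker or Stuart-Maxwell; if a collapse is intended, fix a single cut.

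The cost is a sentence or two in the analysis section and no new data. The Assessment standards section places the blinded reassessment of samples after recruitment ends, and Trial status reports 372 of 408 patients enrolled, so on the article's own timetable the change could precede the reassessed grades.

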## Discussion

The role of EUS-FNA in obtaining cytological materials is well-established [24]. However, a recent study suggests the false positive rate of FNA cytology is 5 % to 7 %, which is higher than the originally reported rates of 0 % to 1 % [25, 26]. Moreover, an increased interest in histological tissue sampling under real-time EUS imaging exists because of the advantage in diagnosing certain suspected tumor types, such as neuroendocrine tumor and lymphomas [27]. A standard 19G FNA needle has been used to obtain histological materials and achieved a diagnostic accuracy of 94.5 % [28], although the device is highly associated with technical failures. A Quick-Core needle was used with an overall diagnostic accuracy of 75 % to 84 % [29, 30]. One drawback of the Quick-Core needle is that it is difficult to maneuver, especially for transduodenal biopsy. Recently, a new 22G needle with a reverse bevel at the tip (EUS-FNB) has become available. The ProCore needle design combines the features of an FNA needle with a core biopsy needle [20], which has enhanced flexibility, especially for core tissue collection. Results from a multicenter study on EUS-FNB showed that, overall, the operations were completed in 98.24 % patients, the histological specimens were adequate in 89.47 % patients, and the diagnoses were accurate in 92.9 % patients [11]. EUS-guided tissue acquisition now seems to be more suitable for histological evaluation [13, 20]. Here, we carry out a randomized controlled trial to compare the diagnostic efficiency of EUS-FNB versus EUS-FNA and to assess the sample quality obtained by different types of needles with different methods. To our knowledge, this is the largest cohort study on EUS-FNB so far. The outcome measurements will help us to understand the special indications for each technique and their diagnostic accuracy. In addition, Aadam et al. reported a significant rescue effect of FNA crossover to FNB [13]. We specifically designed our trial to allow the patient to crossover to the other arm if diagnosis is not achieved after the first round of needle biopsy, which will help us draw our conclusions.

The success of EUS-FNA is associated with several factors, including appropriate methods of biopsy, sample preparation, and onsite cytopathological interpretation [31]. The onsite cytopathological interpretation may not always be available during EUS**-**FNA procedures; therefore, appropriate methods of biopsy and sample preparation are very important. Some echoendoscopists use slow-pull, and others use constant suction. Suction with a self-retracting syringe will likely bring more cellularity but also more blood. In this trial, the echoendoscopist will use both methods (slow-pull and constant suction) on each lesion and, hopefully, will be able to draw a clear conclusion on selecting which biopsy method should be used for which procedure. Furthermore, standard procedures and sample preparation methods will be used to process all types of biopsy samples. For example, after the needle has been inserted into the mass, for both FNA and FNB, the needle will be moved back and forth 20 times within the lesion to collect specimens. The specimens will be expelled from a needle in three steps: step 1, which involves pushing the stylet into the needle; step 2, which involves flushing the needle with 0.1 ml saline; and step 3, which involves filling the needle with 2 ml of air.

Some limitations exist in the present study design. For instance, we will not be performing the rapid onsite evaluation (ROSE) in the current trial. ROSE is most frequently used in the United States, and the absence of an onsite cytopathologist has been shown to affect the diagnostic yield by increasing the number of inadequate samples. Although its popularity is growing here in China as well, several alternative strategies, including the macroscopic onsite evaluation (MOSE), have been reported to improve the diagnostic yield [21]. The well-trained endoscopists in our centers will apply MOSE and gross inspection to evaluate the quality of the specimens. Second, although the crossover design is critical, obtaining agreement from the patients for the second biopsy may be difficult because it may increase the risk of complications. Consequently, the number of patients recruited may be reduced, thereby leading to suboptimal conclusions. Third, some patients may not undergo surgery and, hence, will not have any final pathology report. In addition, the possibility exists that contact with the patient will be lost during the 48 weeks of follow-up. To prevent dropout, local research assistants will be recruited to help complete the patient registration information (record at least two phone numbers) and ensure that appointments are being made for follow-up assessments.

### Trial status

Patient enrollment began on December 20, 2014 and completion is expected by December 31, 2015. At present (December 5, 2015), 372 patients have been enrolled in the study.

## Abbreviations

AFP: Alpha fetal protein
ALP: Alkaline phosphatase
ALT: Alanine aminotransferase
APTT: Activated partial thromboplastin time
AST: Aspartate aminotransferase
BUN: Blood urea nitrogen
CA19-9: Carbohydrate antigen 19-9
CA72-4: Carbohydrate antigen72-4
CEA: Carcinoembryonic antigen
Cr: Creatinine
EUS: Endoscopic ultrasonography
EUS-FNA: Endoscopic ultrasound-guided fine-needle aspiration
EUS-FNB: Endoscopic ultrasound-guided fine-needle biopsy
FNA: Fine needle aspiration
INR: International normalized ratio
MOSE: Macroscopic onsite evaluation
NPV: Negative predictive value
NSE: Neuron specific enolase
PPV: Positive predictive value
PT: Prothrombin time
ROSE: Rapid onsite evaluation
SA: Surface area
SAS: Statistical Analysis System
SSC: Squamous cell carcinoma antigen
TT: Thrombin time
